## Abstract

**Background**: Telenursing comprises a set of tools and interventions enabling nurses to provide remote care. This study aims to assess the impact of telenursing interventions on the supportive care needs of patients with melanoma and lung cancer who are receiving targeted therapies. **Methods**: This six-month monocentric, double-arm, randomised, controlled trial study protocol will assess the effect of telenursing on the supportive care needs (primary outcome) in 40 patients (20 in each group) after one month. The secondary outcomes will be monitored at baseline, one, three and six months: supportive care needs (at three and six months), therapeutic adherence, quality of life, usability and satisfaction, performance status, patient-reported outcomes and main adverse events. The SPIRIT guidelines will be used for the reporting. **Results**: The results from this trial will assess the impact of a telenursing intervention on cancer care. **Conclusions**: This trial could be a starting point for more extensive studies on telenursing interventions to promote nurses’ skills, as well as the quality and safety of care in patients with cancer, highlighting the impact of more outstanding nursing contributions on cancer care. **Trial and Protocol Registration**: The study protocol was approved by the relevant Italian Ethics Committee Lazio Area 5 (RS1851/23, 2773; 6 September 2023) and was registered on ClinicalTrials.gov (trial registry number NCT06254196).

## 1. Introduction

According to the GLOBOCAN 2018 classification [1], lung cancer is the leading cause of cancer mortality, and melanoma is the third most commonly diagnosed cancer in the United States of America (USA) [2]. The study of the molecular characteristics of diseases has allowed targeted therapies (TT) to have more excellent selectivity in terms of the therapeutic target by reducing the traditional toxicities of chemotherapy [3]. The daily home intake of these chemotherapy drugs for a long time is related to the onset of specific adverse events (AEs) and needs. Especially in the first months of treatment, AEs significantly impact patients’ health-related quality of life (HRQoL) [4], sometimes more critically than traditional chemotherapy [5]. Supportive care, which is focused on supporting the complex physical, psychological and social needs related to cancer and its treatments, is considered a practical approach to the adaptation process of patients with cancer [6]. The international literature emphasises the crucial role of the multidisciplinary team, the proactive support of nurses, and the use of patient-reported outcomes (PROs) in improving treatment adherence, early prevention, diagnosis, and correct management of treatment-related AEs, QoL and optimising healthcare resources in cancer care [7,8,9]. Therefore, face-to-face and digital–remote interventions by nurses (telenursing) are recommended to promote cancer patients’ self-care, self-efficacy, clinical outcomes and continuity of care [8,9]. Specifically, telenursing refers to the remote tools and interventions used by nurses to improve the quality of and access to care, communication and exchange of information between healthcare professionals and patients [8]. Lately, in cancer care, several studies have also been conducted using telenursing interventions to manage treatment-related demands and toxicities. In particular, recent studies show that telenursing has a positive impact on the prevention and management of fatigue, anxiety, depression and symptom distress [10,11]. However, despite an increase in telenursing interventions in recent years [12], further studies are needed to test the impact of telenursing interventions on managing patients’ needs, AEs, QoL and PROs [13,14]. A real-time monitoring system could im-prove transitional care, positively impacting the quality of care, patient safety and healthcare resource utilisation [11,15].

To promote the generalisability of the results, considering their incidence and common therapeutic approaches, patients with melanoma and lung cancer were included in this study [16,17].

Furthermore, due to the prevalence and the high burden of lung cancer and melanoma in patients on TT, comparing a telenursing intervention with standard care could highlight its efficacy in cancer care.

### 1.1. Aim

This randomised controlled trial (RCT) study protocol aims to reduce the treatment-related burden of patients with lung cancer and melanoma on TT through increased nursing involvement and the use of telenursing, improving their clinical pathway.

### 1.2. Primary and Secondary Objectives

The objectives of this study will be measured in two compared groups.

Primary objective: To assess the impact of telenursing interventions on the supportive care needs (SCNs) [18,19] in patients with lung cancer and melanoma at the first prescription of TT after one month of treatment (T1). Secondary Objectives: To explore the differences between the AEs reported by healthcare professionals and the patient-reported outcomes and develop a specific nursing reporting system to improve the quality, safety and continuity of cancer care. Further secondary outcomes are shown in Table 1, together with the tools, timing, and users involved in the data collection. Among the secondary outcomes, the SCNs over time (until the end of the study) [18,19], quality of life [20,21], patient satisfaction [22,23], therapeutic adherence [24,25] and performance status [26] will be assessed and compared in both groups. Moreover, the incidence and severity of the following vital signs and adverse events will be compared to highlight the effectiveness of the telenursing intervention with tools based on the Common Terminology Criteria for Adverse Events (CTCAE) [27]: body temperature, blood pressure, heart rate, body weight, pain, stomatitis and mucositis, dysgeusia, nausea and vomiting, diarrhoea, loss of appetite, fatigue, headache, dermatologic reactions, cough and dyspnoea, pain, palmar–plantar erythrodysesthesia, bleeding events, photosensitivity, ophthalmological reactions, sleep, mood and voice disorders.

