They will provide the following:Nursing assessment: to allow comparison between the two groups, the questionnaires described in Table 1 will be used at baseline and according to the timing described in Table 1. The measurements will allow researchers to highlight the effectiveness of the telenursing intervention and the improvement of patients’ clinical path.Support in study procedures: during the 6-month follow-up, nurses will provide advice to the patients involved to improve the experience with the intervention and the tools used, and also in order to optimize the data collection in the two compared groups.Intervention in the IA: with patients involved in the experimental group, research nurses will use telenursing to monitor the supportive care needs and other objectives described in Section 1.2. For the purposes of the study, the telenursing intervention will use the Intelligence2health platform for video calls, a dedicated telephone line, short messages and electronic tools. During the 6-month study, nurses will implement a total of 8 video calls. Nurses will implement patient education interventions to improve patient care, quality of life, satisfaction, treatment adherence, problem-solving skills, and self-care. Suggestions to better manage patients’ needs will be evidence-based and may be agreed with medical oncologists as needed. However, they will be kept constantly updated on the health status of patients. Nursing interventions will be aimed at promoting the care needs of patients.Data collection will be carried out using the chosen tools, according to the timing described in Table 1, at baseline, daily, after 30, 90 and 180 days, to allow comparison between the intervention arm and control arm. In particular, patients and nurses will monitor the burden and needs related to care through the Supportive Care Needs scale [18,19]; therapeutic adherence through the MARS-5I [24,25]; QoL through the QoL SF-36 [20,21]; satisfaction and usability of the system through the SUS [22,23]; performance status through the Karnofsky performance status [26]; and the AEs described in Section 1.2 through the CTCAE tools [27]. Patients enrolled in the control group will use paper questionnaires, while patients in the intervention group will use electronic tools that nurses will check daily to implement any coaching interventions. Any changes in the health status or needs of patients can be intercepted early thanks to the filling out of daily forms by the patients themselves, which nurses will check daily.Creation and management of a specific database.

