#### 2.4.1. Control Arm

The CA patients will attend monthly visits with oncologists and receive in-person nursing care as needed. They will fill out paper-form questionnaires collected by nurses during the monthly visits until the end of the study. Nurses and oncologists will not consider patient data during follow-up, and according to clinical practice, patients should contact oncologists as needed. Data collected by nurses during the monthly visits and by patients at home will be recorded in a specific database by the nurses, but these data will not be evaluated by nurses or oncologists during the study. However, according to current clinical practice, if necessary, patients in the control group will be able to contact oncologists and nurses via the telephone and email addresses provided before the start of the study.

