#### 2.4.2. Intervention Arm

In addition to clinical practice, after the randomisation, the IA patients will receive an educational nurse intervention to improve the SCNs [18,19], prevent the main AEs and recap the study procedures. Furthermore, at baseline, the IA patients will receive the following:A link to access the electronic questionnaires through a web platform (GDPR and privacy compliant) (daily, at one, three and six months).A link to access the platform Intelligence2health [30], actually used in the same national cancer centre for the monthly telenursing interventions.A company telephone number to contact the team nurses.

In the first month, nurses involved in the study will carry out two telenursing interventions through a video call enabled by the platform (Table 2). The first virtual meeting will be conducted seven days after baseline (T0), focusing on the study procedures and e-tools. Subsequent telenursing interventions will be carried out monthly. Research nurses will review the daily data from the IA patients to arrange appropriate reinforcement interventions (coaching), agreed upon with oncologists where applicable. However, the oncologists will be steadily updated on the patients’ clinical conditions. The telenursing interventions will aim to prevent, monitor and improve treatment-related outcomes (Table 1). Specifically, evidence-based nursing coaching interventions will aim to improve the SCNs [18,19], adverse events and vital signs described in the primary and secondary objectives, and what will be required by patients regarding treatment-related needs.

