## Figures and Tables

**Table 1 mps-07-00078-t001:** Outcomes and tools.

Time	User	Outcomes	Tools (Citation)
Monthly	Nurse/Clinician	Adverse events	Common Terminology Criteria for Adverse Events
T0	Nurse	Clinical-anamnestic-demographic data	Registry card
Daily	Patients	Vital signs and main symptoms from patient-reported outcomes	Patient-reported outcomes
T0, T1, T2, T3	Patients	Patient-reported outcomes	Patient-reported outcomes
T0, T1, T2, T3	Nurse/Clinician	Performance status	Karnofsky performance status
T0, T1, T2, T3	Patients	Quality of life	Quality of Life SF-36
T1, T2, T3	Patients	System satisfaction and usability	SUS—System Usability Scale
T0, T1, T2, T3	Patients	Supportive care needs	Supportive care needs
T0, T1, T2, T3	Patients	Therapeutic adherence	MARS-5I

T0: baseline; T1: 30 days; T2: 90 days; T3: 180 days; SF: short form; MARS-5I: Medication Adherence Report Scale Italian.

**Table 2 mps-07-00078-t002:** Participants’ timeline.

Timeline (People Involved)	T0 Baseline	T1 Month 1	Month 2	T2 Month 3	Month 4	Month 5	T3 Month 6

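### Only intervention-arm staff can use patients' daily symptom forms, so the between-arm comparison of clinician-recorded adverse events is confounded with differential ascertainment

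*Protocol article*

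**What the plan says.** All references are to the protocol article.

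- **Discrepancy objective.** Section 1.2 lists among the secondary objectives "To explore the differences between the AEs reported by healthcare professionals and the patient-reported outcomes".
- **Effectiveness comparison.** The same section says, of a list that also takes in vital signs, that "adverse events will be compared to highlight the effectiveness of the telenursing intervention with tools based on the Common Terminology Criteria for Adverse Events".
- **Who records.** Table 1 gives "Common Terminology Criteria for Adverse Events" as a monthly tool with nurse or clinician as the user. Patient-reported outcomes are separate rows completed by patients, daily and at T0 to T3.
- **Intervention arm.** Section 2.4 says that "patients in the intervention group will use electronic tools that nurses will check daily to implement any coaching interventions". Section 2.4.2 repeats the daily review by research nurses and adds that "the oncologists will be steadily updated on the" patients' clinical condition. Video calls, messages and a telephone line are further channels.
- **Control arm.** Section 2.4.1 says of the data gathered at visits and at home that "these data will not be evaluated by nurses or oncologists during the study". Patients may contact staff by telephone or email.
- **Blinding.** Section 2.5 states that neither patients nor professionals are blinded. The article describes no independent AE grading, and no grading made before access to patient reports.

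**The concern.** A count of clinician-recorded AEs depends on how many events occur and on how many the recorder learns about. Here the second component differs by design between the arms. Intervention-arm staff can draw on daily forms and several contact channels. Control-arm staff have the monthly visit and whatever the patient chooses to raise.

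Two results are exposed. In the effectiveness comparison, extra detection adds recorded events to the intervention arm and can offset a real reduction. A null or unfavourable AE result would then be hard to read. In the discrepancy objective, a smaller clinician-versus-patient gap in the intervention arm could arise because the professional had the patient's form to hand, without any change in how symptoms are elicited or judged.

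**Working it through.** **1. The document's own figure.** No AE rate, detection rate or AE sample size is stated. The only calculation (Section 2.2) is for supportive care needs, and it reproduces. SD = sqrt((13.2² + 21.96²)/2) = 18.12 and d = (103.5 − 81.53)/18.12 = 1.21. Power by the noncentral t is 0.893 at 15 per group and 0.913 at 16, so 32 in total, and 32/0.8 = 40. It does not bear on this point except to give 20 patients per arm.

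**2. The asymmetry, side by side.**

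| | Intervention arm | Control arm |
|---|---|---|
| Patient forms | Electronic, checked daily by nurses | Paper, entered in a database, not evaluated |
| Oncologists | Kept updated | Not to consider patient data in follow-up |
| Monthly measurement (Table 2) | Patients, nurses, oncologists | Patients, oncologists |
| Blinded | No | No |

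**3. Effect on recorded incidence.** Let p be the true incidence of one AE and s the share of cases the clinician records, with no false recording. Recorded incidence is p × s. The clinician-versus-patient gap is p × (1 − s), if patients report every case. The recorded risk ratio is therefore the true risk ratio multiplied by (s intervention / s control).

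All values of p and s below are assumptions. The test is Fisher's exact, two-sided 0.05, 20 per arm, by exact enumeration. Control detection is 50% throughout, and p is the same in both arms.

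| True p | s, intervention | Recorded, intervention v control | Gap, intervention v control | Chance of a significant excess in the intervention arm |
|---|---|---|---|---|
| 30% | 70% | 21% v 15% | 9 v 15 points | 0.035 |
| 30% | 90% | 27% v 15% | 3 v 15 | 0.086 |
| 50% | 70% | 35% v 25% | 15 v 25 | 0.059 |
| 50% | 90% | 45% v 25% | 5 v 25 | 0.179 |
| 70% | 70% | 49% v 35% | 21 v 35 | 0.082 |
| 70% | 90% | 63% v 35% | 7 v 35 | 0.291 |

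With equal detection of 50% in both arms the last column would be 0.010 to 0.013.

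**4. Effect on a real benefit.** Take a true reduction from 70% (control) to 40% (intervention).

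- Full detection in both arms: recorded 70% v 40%, chance of a significant benefit 0.347.
- Detection 50% in both: 35% v 20%, chance 0.114.
- Detection 50% control, 80% intervention: 0.70 × 0.50 = 35% v 0.40 × 0.80 = 32%, chance 0.021.

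The recorded ratio in the last case is (0.40/0.70) × (0.80/0.50) = 0.91, against a true ratio of 0.57.

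**The case against.** Five arguments stand on the other side.

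- **The rater is not fixed.** Section 1.2 speaks only of tools based on CTCAE, and Section 2.4 has patients and nurses using them together. Section 2.6 has patients transmitting data on the same AEs. A patient-reported comparison may be what is meant. This stands as an ambiguity. Table 1 nevertheless gives the CTCAE record to nurse or clinician only, so the text needs to say which source carries the effectiveness claim.
- **The order of events is not stated.** That forms are seen before grading is inferred from daily review and monthly recording. The inference is reasonable, but it is an inference.
- **Closer surveillance is part of the treatment.** It is, and a by-arm difference in discrepancy is a legitimate exploratory finding. But recorded CTCAE incidence then measures detection and harm together, which weakens it as evidence of effectiveness.
- **The numbers are small and assumed.** With 20 per arm, even a marked detection difference would usually not reach significance, as the table shows. The issue is bias in the estimate more than false positives.
- **A later analysis plan could handle it.** Only partly. Who sees the forms is settled by the data collection described here, and how an event came to light has to be recorded at the time.

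A reader might also infer that the trial will pool the discrepancy across arms. No section says so, and Section 1.2 opens by placing the objectives in the two groups being compared. Nor can the control arm be taken as two wholly independent reports. Nurses there collect and enter the paper forms, patients can telephone or email, and data that are not evaluated may still be seen.

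**Conclusion.** The concern holds as one of confounding with differential ascertainment in the comparison of clinician-recorded AEs. The probable direction is more recorded events in the intervention arm, which works against showing a benefit. The between-arm contrast in clinician-versus-patient discrepancy is affected in the same way.

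The size cannot be derived from the document. Under the assumed detection rates, equal true incidence appears as an intervention-arm excess of 6 to 28 percentage points, and a true 30-point reduction can shrink to 3 points.

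It would go too far to say that the AE results are driven by ascertainment or cannot be interpreted. No figure shows that the bias dominates, and patient reports collected in both arms allow a cross-check. The primary outcome, patient-reported supportive care needs at one month, and its sample size are not affected. The limitations section does not mention this asymmetry.

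**What to change.** 1. State that the between-arm AE effectiveness comparison uses the patient-reported instrument completed by both arms at T0 to T3. Table 1 names that instrument only in general terms, so confirm that it covers the AEs listed in Section 1.2.
2. Report clinician CTCAE by arm descriptively. Add one field to the AE form in both arms recording whether the event was first identified from a daily form, a call, a message or a visit.
3. Interpret the clinician-versus-patient discrepancy within arm. Treat the control arm as the closest, though not fully independent, estimate for usual practice, and the intervention arm as agreement when forms are shared.
4. Reconcile Sections 2.4, 2.4.1 and 2.5 with Tables 1 and 2 on who records AEs in the control arm. Section 2.4.1 has nurses collecting data at monthly visits and Section 2.5 has them involved with both groups' toxicities, while Table 2 leaves nurses out of control-arm measurement.

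The cost is some wording and one data field. The downsides are real. Each discrepancy estimate rests on about 20 patients. Patient reporting is unblinded and still differs by arm in mode (paper against electronic) and in coaching. Events falling between the T0 to T3 assessments may be missed. The change therefore reduces the bias and does not remove it.

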### 2.6. Data Collection

The planning of the study will include an enrolment period lasting 12 months, starting from the involvement of the first patient after 15 June 2024. The study follow-up will last six months. After this period, all the patients will be referred to current clinical practice. Nurses will record digital data from patients’ self-reports and nurses’ interviews and observations in a specific database.

Patients in the control arm will be treated according to current clinical practice, mainly with the support of oncologists. The paper questionnaires that patients and nurses will complete during the study will be recorded by nurses in a specific database.

Data from patients enrolled in the intervention group will be collected via electronic questionnaires, similar to those of nurses. Data collection for the outcomes described in Table 1 will be assessed at baseline (T0), after 30 (T1), 90 (T2) and 180 days (T3). In addition, patients will transmit data daily relating to the monitoring of vital parameters and AEs described in the section on the primary and secondary objectives.

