### 2.7. Data Analysis

Intention-to-treat analysis will be applied in case of abandonment of a patient from one arm or the other. The rigor observed in the study will be aimed at acquiring detailed and exhaustive information. However, missing data due to incomplete or partial registration by the patient will be treated with appropriate statistical techniques. Descriptive statistics will explore the continuous variables through the means and standard deviations (±SD), while the categorical variables will explore the absolute frequencies and percentage values. The Kolmogorov–Smirnov normality test will be used for all the continuous variables. The Chi-square or Fisher’s exact test will assess the potential associations between categorical variables. The differences for continuous variables will be explored using the nonparametric Mann–Whitney U test or Student’s *t* test, depending on the nature of the distributions of the variables examined. All the statistical analyses will be performed using Statistical Package for the Social Sciences (SPSS) Software 29.0 (IBM SPSS Statistics for Windows, Version 29.0. Armonk, NY, USA: IBM Corp.) for Windows. A *p*-value < 0.05 will be considered statistically significant.

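### None of the tests named in Section 2.7 fits the first secondary objective, which compares clinician and patient adverse event reports within the same patients

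*Protocol article*

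**What the plan says.** Section 1.2 names as the first secondary objective "To explore the differences between the AEs reported by healthcare professionals and the patient-reported outcomes", and links it to developing a nursing reporting system. In Table 1, nurses or clinicians record adverse events monthly with the CTCAE, and patients give their own reports daily and at T0, T1, T2 and T3. Both sources describe the same people.

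Section 2.7 gives the tests. For categorical data, a chi-square or Fisher's "exact test will assess the potential associations between categorical variables". For continuous data, "The differences for continuous variables will be explored using the nonparametric Mann–Whitney U test or" Student's t, depending on the distribution; the t test is not called paired. The significance rule is a p-"value < 0.05 will be considered statistically significant". No paired test, agreement measure or repeated-measures model is named. On missing data, "missing data due to incomplete or partial registration by the patient will be treated with appropriate statistical techniques".

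For the scales, Section 1.2 lists "the SCNs over time (until the end of the study") as a secondary outcome to be compared between arms, the Abstract words it as "supportive care needs (at three and six months"), and Section 2.6 says that outcomes "will be assessed at baseline (T0), after 30 (T1), 90 (T2) and 180 days (T3").

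**The concern.** A clinician's and a patient's report of the same symptom in the same person are a matched pair. The question is whether one source records more events than the other, and by how much. The categorical tests named in Section 2.7 could be used on such data in two ways, and neither answers it.

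- **Reports as two groups.** The test treats one patient's two reports as coming from two independent people. When the reports are positively correlated, its standard error is too large, so a real gap is easily missed.
- **Reports as a cross-table.** The test asks whether the two sources are related. They can be strongly related while clinicians miss many events.

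At stake is the result meant to inform the nursing reporting system. Under-reporting could be called absent, or a strong association could be taken as reassurance.

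A lesser matter concerns the scales measured at T0 to T3. A test at one visit uses neither the baseline value nor the other visits.

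**Working it through.** **Sample size, to see whether it is touched.** Section 2.2 gives means 81.53 (SD 13.2) and 103.5 (SD 21.96), two-sided 5% and 90% power. Pooled SD = √((13.2² + 21.96²)/2) = 18.12. Effect size = 21.97/18.12 = 1.21, as stated. The noncentral t distribution gives 89.3% power at 15 per arm and 91.3% at 16, hence 32 patients, and 32/0.8 = 40. The calculation rests only on the one-month score and reproduces.

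**One worked table.** The article gives no report rates, so these counts are assumed: 40 patients, of whom 11 have the symptom on both reports, 9 on the patient's only, 1 on the clinician's only and 19 on neither. Patients report 20/40 and clinicians 12/40.

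- Unpaired chi-square: pooled proportion 32/80 = 0.4; 0.20²/(0.4 × 0.6 × 2/40) = 3.33, p = 0.068. Fisher p = 0.110.
- Exact McNemar on 9 v 1: 2 × (1 + 10)/2¹⁰ = 22/1024, p = 0.0215.
- Paired difference: 8/40 = 0.20; SE = √(10 − 8²/40)/40 = 0.072; 95% CI about 0.06 to 0.34. The unpaired SE is √(0.5 × 0.5/40 + 0.3 × 0.7/40) = 0.107, giving −0.01 to 0.41.
- Association chi-square on the cross-table: 40 × (11 × 19 − 9 × 1)²/(20 × 20 × 12 × 28) = 11.9, p = 0.0006.
- Kappa: observed agreement 30/40 = 0.75, chance agreement 0.5 × 0.3 + 0.5 × 0.7 = 0.50, so (0.75 − 0.50)/0.50 = 0.50.

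One data set thus yields no significant difference, a significant difference, or a strong association, while clinicians miss 9 of the 20 patient-reported events (45%).

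**A range instead of one table.** Simulation, 20,000 runs, 40 patients; report rates and within-patient correlation (phi) are assumed. The first two result columns use equal rates of 40%; the last three use 30% v 50%.

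| phi | Unpaired chi-square, false positives | Association test rejects | Unpaired power | McNemar power | Exact McNemar power |
|---|---|---|---|---|---|
| 0 | 5.2% | 4.9% | 46% | 45% | 35% |
| 0.3 | 2.1% | 48% | 45% | 57% | 48% |
| 0.5 | 0.6% | 91% | 44% | 73% | 63% |
| 0.6 | 0.3% | 98% | 42% | 87% | 75% |

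At equal rates, McNemar's asymptotic form rejects 4.3–5.3% of the time. Its exact form is itself conservative, at 1.9–3.2%.

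**Scales over time.** The arms are independent samples. Simulated per-visit t tests with 16 per arm reject 4.9–5.3% of the time under no effect, so each is valid. What they forgo can be sized by an assumption: if baseline and follow-up correlate at r, adjusting for baseline multiplies the residual variance by 1 − r². For r of 0.3, 0.5 and 0.7 that is 0.91, 0.75 and 0.51, a reduction of 9%, 25% and 49%.

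**The case against.** Section 2.7 lists its tests in general terms, does not say they are exhaustive, and assigns none to the clinician–patient comparison. The article condenses a fuller plan, and a separate analysis plan may name further methods. Section 1.2 says its objectives are measured in two compared groups, and the listed tests do suit between-arm comparisons of adverse event incidence. The objective is only to explore, and plain frequencies would already show under-reporting. Much of this stands: a reader might infer that no other method will be used, and the text does not say so. What remains is that the article gives a specific list, and nothing on it answers an objective that it names.

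A reader might also infer that supportive care needs over time would be analysed wrongly, or that patients with a missed visit would be dropped. The documents support neither. The Abstract words the outcome as values at months three and six, per-visit tests between randomised arms keep their level, and Section 2.7 states intention-to-treat and does not commit to complete cases.

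The worked table is also fragile. Split by arm, with discordant pairs of 5 v 0 and 4 v 1, exact McNemar gives 2/2⁵ = 0.0625 and 2 × (1 + 5)/2⁵ = 0.375. This is a reason to pool the arms for the test, not to ignore the pairing. Finally, the patient tool's grading scale is not visible in Table 1, so weighted kappa may not be possible.

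**Conclusion.** The point holds for the clinician–patient comparison. The named tests either ignore the pairing or answer a different question. For positively correlated reports the consequence of the unpaired test is conservatism and lost power: about 42–45% against 57–87% (48–75% with the exact test) under the assumed rates and phi of 0.3 to 0.6. The unpaired test does not produce an excess of false claims of difference. If the reports were uncorrelated, little would be lost. Mistaking association for agreement is the separate risk.

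For the scales there is no error to correct, only precision to gain, and its size depends on a correlation that the article does not give. The primary outcome and the sample size of 32 evaluable and 40 enrolled are unaffected.

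**What to change.** In Section 2.7, for the clinician–patient objective:

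- for each symptom at matched visits, report the paired difference in proportions with a 95% confidence interval and McNemar's test, pooled over arms;
- show by-arm results descriptively. Nurses review the daily patient reports in the intervention arm only, so the two sources may agree more closely there;
- add kappa for agreement, weighted only if both reporters use the same ordinal grade;
- label the whole analysis exploratory. Section 1.2 lists roughly 20 signs and symptoms, and four visits would make about 80 comparisons at an unadjusted 5% level.

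As an improvement, for supportive care needs, SF-36, MARS-5I and Karnofsky, fit a mixed model with arm, visit, arm-by-visit and baseline, and report the arm difference at each visit. The downside is reliance on model assumptions with about 16 to 20 patients per arm, so keep the rank test as a sensitivity analysis if residuals are clearly non-normal.

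The cost is a few sentences. The measurements are already scheduled, except that weighted kappa depends on a common grade, and the methods are available in the planned software.
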